## Abstract

**Background:**

Individuals diagnosed with autism spectrum disorder (ASD) experience impairing challenges in social communication and interaction across multiple contexts. While social skills group training (SSGT) has shown moderate effects on various sociability outcomes in ASD, there is a need for (1) replication of effects in additional clinical and cultural contexts, (2) designs that employ active control groups, (3) calculation of health economic benefits, (4) identification of the optimal training duration, and (5) measurement of individual goals and quality of life outcomes.

**Method/design:**

With the aim of investigating the efficacy and cost-effectiveness of a SSGT, KONTAKT©, a two-armed randomized control trial with adolescents aged 12–17 years (*N* = 90) with ASD and an intelligence quotient (IQ) of over 70 will be undertaken. Following stratification for centre and gender, participants will be randomly assigned to either KONTAKT© or to an active control group, a group-based cooking programme. Participants will attend both programmes in groups of 6–8 adolescents, over 16 one-and-a-half-hour sessions. The primary outcome examined is adolescent self-rated achievement of personally meaningful social goals as assessed via the Goal Attainment Scaling during an interview with a blinded clinician. Secondary outcomes include adolescent self-reported interpersonal efficacy, quality of life, social anxiety, loneliness, face emotion recognition performance and associated gaze behaviour, and parent proxy reports of autistic traits, quality of life, social functioning, and emotion recognition and expression. Cost-effectiveness will be investigated in relation to direct and indirect societal and healthcare costs.

**Discussion:**

The primary outcomes of this study will be evidenced in the anticipated achievement of adolescents’ personally meaningful social goals following participation in KONTAKT© as compared to the active control group. This design will enable rigorous evaluation of the efficacy of KONTAKT©, exercising control over the possibly confounding effect of exposure to a social context of peers with a diagnosis of ASD.

**Trial registration:**

Australian New Zealand Clinical Trials Registry (ANZCTR). ACTRN12617001117303. Registered on 31 July 2017. anzctr.org.au

ClinicalTrials.gov, NCT03294668. Registered on 22 September 2017. https://clinicaltrials.gov

## Background

### Autism in adolescence

Autism spectrum disorder (ASD) is a condition of neurodevelopmental origin, presenting early in life [1]. Hallmark features of ASD include persisting challenges in social communication and interaction across multiple contexts, and restricted repetitive patterns of behaviour, interests, or activities, leading to qualitative impairment in significant areas of life [1, 2]. In 2015, it was estimated that approximately 0.6% of Australians had an ASD diagnosis, representing a 42.1% relative increase in prevalence from 2012 [3]. Prevalence rates vary across age groups, with the prevalence among Australian adolescents estimated to range from 3% to 4% [3]. The rising diagnostic trends for ASD among children over recent decades have seen an unprecedented number of adolescents with ASD, resulting in an urgent need for evidence-based interventions aimed at improving outcomes for these young people [4].

Adolescence is a time when social demands escalate as peer networks become increasingly important [5, 6]. Contrary to popular belief, most individuals with ASD might accurately perceive their level of social interaction and communication abilities and their limitations in networking with their peers [7]. The social difficulties associated with ASD during puberty [8], compounded by common comorbidities such as social anxiety, mean adolescence can be a particularly difficult period for these young people [9]. While impairments in daily functioning are central to a diagnosis of ASD [1], in adolescence it can have the complication of hampering the transition to adulthood, reducing adolescents’ desire for independent living and limiting education and employment outcomes [10, 11]. The cumulative impact of these experiences is evident in the poor quality of life outcomes observed during this period [12].

### Social skills group training

It has been argued that underpinning the core challenges of ASD is a paucity of social understanding [13, 14]. Social skills training, that is overtly teaching social skills, has been proposed as one means of ameliorating the difficulties of adolescents with ASD [15] with evidence showing a positive impact on social skills [16–18], anxiety [9, 19, 20], and family quality of life [21]. It is likely that participating in social skills training early in life will lessen and possibly even prevent social difficulties later in life [22].

While social skills training interventions can be delivered to individuals or groups, the group context has many apparent benefits for adolescents with ASD, including providing an in-vivo and immediate context for practising learnt skills and the opportunity for positive interactions with peers [7]. Social skills group training (SSGT) interventions for adolescents diagnosed with ASD are commonly delivered in small groups of 4–9 participants [16, 17, 20, 23–25] with intelligence quotients (IQs) of > 70, and led by one to three SSGT facilitators [15, 19]. Sessions aim to teach a range of skills promoting social communication and interaction skills, covering topics such as emotion recognition, assertion, initiation, interpretation of verbal and non-verbal cues, conflict management, coping strategies, self-control, cooperation, developing and maintaining a relationship, and strategies for handling bullying, rumours, and gossip [19, 24, 26].

A search of the current literature evaluating SSGTs for adolescents via randomized controlled trials (RCTs) identified a number of design and intervention limitations. Consistent design limitations included small sample sizes [9, 27–31], failing to employ blinded or external observer-report measurement of dependent variables [17, 20, 27, 29, 30, 32–35], failing to describe the randomization processes [27, 29–31, 33, 34] or employ allocation concealment [17, 20, 27–36], limited application of intent-to-treat data analysis [17, 27–30, 32–35], a lack of clarity in regard to compliance with the Consolidated Standards of Reporting Trials (CONSORT) statement [20, 27, 29, 30, 35, 36], and limited examples of mixed methods studies integrating quantitative and qualitative data collection methods and analysis in understanding the outcomes of interventions [17] (Additional file 1 and Additional file 2).

A range of identified intervention shortcomings included limited consideration or incorporation of adolescents’ personal goals [20, 27–31, 33, 34, 36], outcomes largely measured by parent proxy report [17, 28, 29, 31, 32, 35, 36], inadequate tailoring of interventions to individual activity preferences [20, 29, 30, 33–36], failing to consider the relationship between intervention dosage (that is the number of sessions) and outcomes [20, 27–31, 33–36], the absence of cost analysis [17, 20, 27–36], and limited reporting of adverse events during the intervention period [20, 27–30, 32–34, 36] (Additional file 1). While comparison groups varied considerably, most examined the efficacy of SSGT interventions relative to usual care waitlist control groups, with limited description of what interventions and therapies were received by comparison groups. To date, only three studies have compared the efficacy of SSGT interventions against an active control group [29, 30, 36], limiting understanding of the influence of confounding factors, such as exposure to social context, on the outcomes of SSGT interventions. As a result, it remains unknown whether the benefits of receiving a SSGT intervention result from significant exposure to a peer group or whether they can be attributed to the social skills training and psychoeducational components of these interventions.The perceived benefits of SSGT interventions from the perspective of the adolescents themselves in achieving their personally meaningful social goals has yet to be rigorously evaluated. While it is likely that researchers have been reluctant to focus on adolescent-determined personally meaningful outcomes, given the inherent difficulty adolescents with ASD experience in self-reporting their own and perceiving other’s emotional states [37, 38], there is a clear over reliance on parent proxy reports in research evaluating the efficacy of SSGT programmes [9, 17, 24, 35]. This is of particular concern given the level of discrepancy between adolescent self-report and parent proxy report ratings in the domains of emotional and social functioning [39]. The role of SSGT programmes in supporting the achievement of personally meaningful social goals of adolescents diagnosed with ASD remains unknown.

### Present study

While the KONTAKT© SSGT programme is designed for both children and adolescents, the present study will evaluate the efficacy of KONTAKT© in Australian adolescents. KONTAKT© originated in Germany [40–42], and was subsequently further developed and evaluated in Sweden via RCTs [17, 32]. In Sweden, the efficacy of KONTAKT© was examined in comparison to a treatment-as-usual control group receiving ongoing treatment only. Swedish adolescents receiving 12 sessions of KONTAKT© demonstrated improvements in social skills, particularly in girls, and improvements in adaptive behaviours as reported by parents immediately following the intervention [19]. Adolescents receiving the longer 24-session version of KONTAKT© demonstrated greater effects [32] than those receiving the 12 sessions, with effect sizes of 0.8 and 0.3 observed for the long and short versions, respectively, for the primary outcome measure [17].

As ASD is primarily associated with challenges in social skills functioning in a given context, it is critical that any social intervention considers the role of culture [43, 44]. To be truly effective, social skills training interventions must be tailored to reflect the cultural norms of a target group [45]. Given the cultural similarities between Sweden and Australia [46], it was deemed likely that KONTAKT© would be similarly effective in improving the social skills of Australian adolescents with ASD as it had been for their peers in Sweden. While the majority of the content of KONTAKT© was potentially directly transferable to the Australian context, in adapting it for the Australian context it was firstly translated from Swedish to English and modified for obvious cultural differences.

Given the findings from KONTAKT© evaluation studies in Sweden demonstrating that the 24-session version was significantly more effective for adolescents with ASD than the shorter 12 session version, a finding linked with the opportunity to participate in more individualized sessions and opportunities to practise skills [47], it was initially envisaged that the Australian evaluation would employ an adapted 24-session version. However, following consultation with Australian service providers and clinicians, it was determined that given the structure of the Australian school year, which is roughly standardised nationally to run across four terms of approximately 10 weeks each, a 16-session version of KONTAKT©, involving eight sessions per term across two consecutive school terms would be more feasible. The feasibility and acceptability of the 16-session version of KONTAKT© was assessed and demonstrated to be favourable in a pilot study (under review). This pilot study provided feasibility and preliminary evidence of the potential efficacy of the 16-session programme, supporting the achievement of the personal meaningful social goals of Australian adolescents with ASD (*p* < 0.001) immediately after the programme had ended. Based on the results from the pilot study, KONTAKT© was further refined in a collaboration between Swedish and Australian clinicians and researchers, and Australian adolescents with ASD and their parents. This process resulted in a standardised version of KONTAKT© for an Australian context in preparation for evaluating its efficacy in an RCT.

## Methods

### Aim

This protocol aims to employ an RCT design to rigorously evaluate the efficacy of KONTAKT© in supporting the attainment of personally meaningful social goals of adolescents with ASD. The design of this study will address many of the noted limitations of previous SSGT evaluation research, including implementation of a manualised intervention KONTAKT©, controlling for social context, employing a primary outcome measure with adequate power to assess the achievement of adolescents’ personally meaningful social goals, undertaking a cost utility analysis, and investigating the relationship between dose (number of sessions) and the response of adolescents with ASD to a SSGT intervention. The study design stipulates clear inclusion and exclusion criteria, standardised outcomes measures validated for use with adolescents with ASD, blinded assessment of outcome measures, and stratified randomization. This study seeks to answer two research questions (1): can KONTAKT© make a unique contribution to facilitate achievement of adolescents’ personally meaningful social goals above and beyond any support provided by the positive social context? (2) Is KONTAKT© cost-effective in comparison to an active control condition?

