### Sample size calculations

The KONTAKT© study in Sweden (both 12-week and 24-week versions) employed the Social Responsive Scale - second edition (SRS-2) as the primary outcome measure. Based on an effect size of 0.54, derived from roughly averaging the effect size (ES) as measured by the SRS-2 from trials examining the efficacy of the long 24-session (ES = 0.76) and the short 12-session (ES = 0.32) versions of KONTAKT© at post-test, and applying multivariate analysis of variance (MANOVA) for repeated measures (within-between interactions) at the three time points (using the intent-to-treat approach), a minimum of 57 participants are required (as calculated by G*Power [53] with power of 0.95 at a conventional error probability (α = 5%)). However, unlike the Swedish study, the present study will employ the Goal Attainment Scaling (GAS) as the primary outcome. It has been argued that GAS has good reliability when used as an outcome measure with interventions for adolescents with ASD [54–56]. Further, unlike previous investigation of KONTAKT© [17, 32], the current study will compare this SSGT efficacy against an active control group, to control for exposure to a social context with peers with ASD. It is likely that both these factors will have a limiting impact on the power of the study, and as such we will aim to recruit a sample of at least 90 participants into this study, increasing the likelihood of detecting possible effects [19]. This sample size will also account for an attrition rate of 37%, which is larger than what is expected based on the previous KONTAKT© studies.

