### Secondary outcome measures

The Social Responsiveness Scale - Second Edition (SRS-2) standard version is a 65-item parent rating scale, designed to measure autistic-like traits in individuals aged 4–18 years. The SRS-2 enables calculation of a total score and five subscales: social awareness, social cognition, social communication, social motivation, and restricted interests and repetitive behaviour. The scale is scored on a 4-point Likert scale, ranging from “not true” (0) to “almost always true” (3). Scores range from 1 to 195 with the expected value for individuals with a primary diagnosis of ASD being approximately 100 [61]. Previous studies in individuals with ASD show good psychometric properties for SRS-2 (internal consistency of 0.9) [62, 63]. As recommended for research, the raw scores of the measure (total and subscale) will be used in this study [63].

The Circumplex Scale of Interpersonal Efficacy (CSIE) [64] measures an individual’s confidence in their ability to successfully perform behaviours associated with each facet of the interpersonal circumplex (assert, distance, yield, and connect). Each octant scale shows a progressive blend of two axial dimensions (e.g. “speak up” representing an assertive action, “get them to leave me alone” a distancing action, and “tell them when I am annoyed” combining these two actions) [65]. As suggested by previous research, this study will use these dimensional scores instead of the eight octants to predict the outcome [66]. Previous studies in adolescents with ASD have demonstrated acceptable internal consistency of 0.78 for this measure [64].

The Perth Aloneness Scale (PLS) is a self-report measure consisting of 24 statements such as “I feel left out of things at school”, or “I get along with my classmates”, measuring four dimensions of loneliness in young people (isolation, friendship, and positive and negative attitudes toward solitude) [67–69]. Responses are recorded on a 6-point Likert scale indicating agreement with a statement, ranging from “never” (1) to “always” (6), with higher scores suggesting higher levels of loneliness and negative attitude towards solitude. This scale has yielded good reliability for the overall scale and subscales (Cronbach’s alpha = 0.84). The use of the scale in the current study is further supported by established norms for Western Australian adolescents [67].

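### The Aim claims adequate power on the primary outcome, but the only power calculation is for SRS-2 against usual treatment; no figure supports power on GAS against an active control

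*Protocol article*

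**What the plan says.** The Aim section presents the trial as correcting weaknesses of earlier social skills studies. One listed feature is "employing a primary outcome measure with adequate power to assess the achievement of" the adolescents' own social goals. The outcome that measures those goals is GAS.

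The section on sample size calculations starts from the Swedish trials, which "employed the Social Responsive Scale - second edition (SRS-2) as the primary outcome measure". The input is stated as follows: "Based on an effect size of 0.54, derived from roughly averaging the effect size (ES) as measured by the SRS-2 from trials" of the 24-session version (0.76) and the 12-session version (0.32), both at post-test. A repeated-measures MANOVA with three time points, power 0.95 and α = 5% then gives a minimum of 57 participants.

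The same section notes that, unlike those trials, "the present study will employ the Goal Attainment Scaling (GAS) as the primary outcome", and that the comparator is now an active control group. It goes on: "It is likely that both these factors will have a limiting impact on the power of the study". The response is to recruit at least 90. The section adds that 90 also covers attrition of 37%, which it describes as more than the earlier studies would lead one to expect.

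Elsewhere in the protocol:
- Under Secondary outcome measures, the SRS-2 "standard version is a 65-item parent rating scale".
- Under Present study, the Swedish comparator is given as treatment as usual.
- Under Design, the primary endpoint is the follow-up 12 weeks after the intervention.
- Under Present study, the pilot is credited with "supporting the achievement of the personal meaningful social goals of Australian adolescents with ASD", with p < 0.001 straight after the programme. No effect size or SD is given.

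**The concern.** The Aim states a property of the design without qualification. The section that should demonstrate it sizes the trial on another outcome, another rater, another comparator and another time point, and then says that two of those changes will probably reduce power. No GAS mean, SD or between-arm difference appears anywhere in the article.

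The first research question is whether KONTAKT adds anything to the benefit of a positive social setting. If the GAS comparison is null, a reader who relies on the Aim could take it as evidence of no added benefit from an adequately powered trial. The protocol gives no basis for saying how large a GAS difference could have been missed.

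**Working it through.** **1. The plan's own figure.** Inputs, all from the sample size section: effect sizes 0.76 and 0.32, two groups, three time points, power 0.95, α = 0.05.

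- Average effect: (0.76 + 0.32) / 2 = 0.54.
- MANOVA within-between interaction with 0.54 entered as f(V): df1 = 2, df2 = N − 3, noncentrality λ = N × 0.54².
- N = 56: power 94.97%. N = 57: λ = 57 × 0.2916 = 16.62, power 95.3%.

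The minimum of 57 reproduces exactly.

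**2. What that figure refers to, beside the primary analysis.**

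| | Behind 57 / 0.95 | Primary analysis |
|---|---|---|
| Outcome | SRS-2, parent-rated | GAS, self-rated in an interview with a blinded assessor |
| Comparator | Treatment as usual | Cooking group (active control) |
| Time of effect | Post-test | 12-week follow-up |

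None of the three rows matches.

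**3. What the increase to 90 buys.**

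- Completers at the stated attrition: 90 × (1 − 0.37) = 56.7, or about 57.
- In reverse: 57 / 0.63 = 90.5, which rounds up to 91.

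The step from 57 to 90 is thus almost exactly the attrition allowance. At 37% attrition it leaves no reserve for the change of outcome or comparator. With lower attrition some reserve remains, but the protocol does not quantify it.

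**4. What 90 and 57 participants can detect (illustration).** Assumptions: two-sided 5% two-sample t-test at a single visit, 1:1 allocation, no clustering, no covariate adjustment. Power comes from the noncentral t distribution with noncentrality d × √(n/2), n per arm, solved for d.

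| Participants | n per arm | d at 80% power | d at 95% power |
|---|---|---|---|
| 90 | 45 | 0.60 SD | 0.77 SD |
| 57 | 28.5 | 0.76 SD | 0.97 SD |

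Turning these into GAS points needs an SD, and the article gives none. With an assumed SD of 0.8 to 1.2 points, 80% power corresponds to:

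- 90 participants: 0.597 × 0.8 = 0.48 to 0.597 × 1.2 = 0.72 points.
- 57 participants: 0.755 × 0.8 = 0.60 to 0.755 × 1.2 = 0.91 points.

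One point is a full step on the GAS scale.

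**The case against.** The best defence is disclosure. The sample size section names the SRS-2 source, the switch to GAS and the active comparator, warns that power will probably suffer, and raises the target. Borrowing from the nearest trials of the same programme is common when no between-arm estimate exists on the new outcome. This stands as far as it goes: nothing is hidden. But the Aim does not carry the caveat, and the increase offered in response is the same margin assigned to attrition.

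The phrase in the Aim could also be read as describing the measure's capacity to capture personal goals rather than statistical power. That reading is possible. However, the Masking and blinding section calls for adequately powered studies, which makes the statistical sense plausible, and the article gives no figure for the other sense either.

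The illustration in step 4 is not the planned analysis, which is a random effects regression on repeated GAS scores adjusted for age, IQ, gender, centre and comorbidity. This is correct, and is why those values are offered only as an illustration.

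Three stronger readings are tempting, and the document does not support them:
- **That the trial is underpowered on GAS.** Without a GAS effect or SD, power on GAS cannot be calculated in either direction.
- **That 57 is miscalculated.** It reproduces with 0.54 as f(V). The article says only that 0.54 is an effect size, so whether f(V) is the right scale for it cannot be settled from the text.
- **That the pilot p-value implies a GAS effect size which should have been used.** The article does not name GAS, the test or the number analysed for that result. It describes no control group, so the p-value could not supply a between-arm effect.

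**Conclusion.** The concern holds as an unsupported power claim, not as an arithmetic error. The Aim asserts adequate power on the primary outcome. The only figure offered, 57 participants at power 0.95, applies to post-test SRS-2 effects against usual treatment, and the sample size section expects the change of outcome and comparator to lower power. At the stated 37% attrition, 90 recruits become about 57 completers and nothing is left to offset that loss.

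The mismatch and the attrition arithmetic rest on the protocol's text alone. The detectable differences (0.60 and 0.76 SD at 80% power, 0.77 and 0.97 SD at 95%) rest on the simplifying assumptions in step 4, and the values in GAS points also rest on an assumed SD. They show what the trial could detect under those assumptions; they do not establish a shortfall.

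**What to change.** 1. In the Aim, remove the adequate-power wording, or qualify it by pointing to the caveat in the sample size section.
2. In the sample size section, state that 57 / 0.95 applies to SRS-2 against usual treatment and is not the power of the primary GAS analysis.
3. In the same section, give the standardised arm difference at the 12-week follow-up that can be detected with 90 and with 57 participants, with the assumptions stated. The figures in step 4 can serve as the illustration.
4. If the difference is also expressed in GAS points, label the SD as an assumption and show a range. A pilot SD, if one exists, would come from post-programme, single-arm data. It need not apply at the 12-week follow-up or in the cooking group, and it also carries the sampling error of a small pilot.

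The cost is wording in two sections and a short calculation. Recruitment, allocation, outcomes and analysis do not change. The downside is that the stated power position becomes less favourable.
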